The principle of universalism in the allocation of social benefits, that is the availability of social benefits to everyone as of right, is contrasted with allocation on a selective basis (targeted) in which benefits are allocated on the basis of need as determined by means testing of income.^33^ The advantage of universal benefits is that they are easy to administer and can be efficiently delivered. The major disadvantage is that they are expensive, because they are delivered to those who do not need them as much as to those who do. However, the use of targeting involves some mechanism that discriminates between the poor and the non-poor. As such it always runs the danger of committing either type I errors which occur when someone who deserves the benefits is denied (underpayment, false positives), or type II errors, which occur when benefits are paid to someone who does not deserve them (overpayment, leakage).^34^ The HiP grant represented an attempt to influence behaviour—appropriate and timely receipt of antenatal care advice—by means of a relatively modest, universally applied cash transfer. The evaluation of the effectiveness of such a payment may inform other policies aiming to change behaviour.

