### Study population

The population under study will be all singleton births in Scotland over the periods of January 2004 to March 2009 (preintervention), April 2009 to April 2011 (intervention) and May 2011 to December 2013 (postintervention).

The Scottish maternity and neonatal database is a comprehensive record linkage system.^40^
^41^ Probabilistic linkage procedures are used to add a unique identifier to all data sets to ensure all relevant records relating to an individual can be linked as required. It facilitates the linkage of a number of records from the system of Scottish Morbidity Records (SMR) including mother's obstetric records (SMR02) and the baby's birth and neonatal information from Scottish Birth Records (SBR).^42^ Further links to the stillbirth and infant Death Survey and the National Records of Scotland (NRS) birth, stillbirth and infant death records can be carried out. The coverage is almost all births in Scotland.^43^ From NRS data, we know of all registered births in Scotland (ie, 100%). We have suitable record linked data on 98% of these births.^44^ These will nearly all be hospital births; a fairly high proportion of the missing records are home births.

There is an average of about 56 000 births per year in Scotland.^45^ The analysis period 2004–2013 should yield over 585 000 births. The analysis period 2006–2013 should yield over 455 000 births.

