#### Secondary outcomes

The following secondary outcomes will be assessed:
Gestation at booking;Booking before 25 weeks;Measures of size: crown to heel length, head circumference;Measures of stage: gestational age at delivery, weight-for-dates (standardised; SGA babies are those weighted less than the 5th centile weight, or LGA weighted more than the 90th centile weight), term at birth (preterm, babies are born at less than 37 weeks gestation; term babies are those born between 37 and 42 weeks gestation and post-term babies are born after 42 weeks gestation);Birth outcomes: mode of delivery, stillbirths, neonatal deaths, 5 min Apgar score. Although there is some debate concerning the robustness of the Apgar score as an outcome, it is in common use and we will therefore present results for this outcome within the context of the wide debate on the subject.

Due in part to the introduction of smoking ban in Scotland in 2006, an additional outcome of interest is maternal smoking. Maternal smoking is collected at booking and during pregnancy. The health advice given when receiving the HiP grant might have an impact on smoking rates during pregnancy over and above that of the smoke-free legislation. We will analyse the temporal change in smoking rate by socioeconomic class and its effect on outcomes.

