### Data analysis plan

#### Statistical analysis

Descriptive statistics of all variables will be presented as mean, SD, minimum, median and maximum for continuous variables and as proportions when the variables are categorical.

The main statistical design we will use is interrupted time series.^64^ Segmented regression analysis will allow an estimation of the size of the effect of the HiP grant at different time points, as well as changes in the trend of the effect over time after its implementation.

Outcomes will be measured on individual births, which are nested within mothers, with mothers themselves clustered within data zones and Health Boards. Multilevel univariable and multivariable models will be used to determine whether the outcomes changed during the period in which the HiP grants were in effect. Multilevel linear regression will be used when the outcome is continuous and multilevel binomial logistic regression when the outcome is dichotomous. Multilevel multinomial logistic regression will be used for the multicategory outcomes mode of delivery and 5 min Apgar score.

All analyses will be adjusted for temporal trends and seasonal variations in outcomes in addition to maternal age, sex of child, parity, marital status, height, weight at booking, diabetes, smoking status, gestation at booking, maternal diabetes, social class, maternal smoking and area deprivation.

The effect of HiP grant on birth weight might have a carryover effect after the withdrawal of the grant. In other words, postintervention the slope in birth weight might not fall back to the same rate as preintervention. This could be due to women who have gave birth during the intervention subsequently having a birth postintervention but still heeding the health advice given during their first pregnancy. We will carry out an additional analysis only on primiparous women to avoid such contamination.

We will analyse preterm births stratified by mode of delivery and stratified according to whether the birth was induced or spontaneous.

We will repeat the main analyses including (ie, adjusting for the effect of) ethnicity along with other covariates and compare the results with analyses excluding ethnicity to gauge the impact of this on our results. We note that the quality of this variable (including the completeness of recording) is poorer than for other variables and that only 1–2% of mothers delivering in Scotland are from minority ethnic backgrounds.

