^66^ According to Rothman,^65^ reducing the type I error for null associations increases the type II error for those associations that are not null. He recommends a policy of not making adjustments for multiple comparisons because it will lead to fewer errors of interpretation when the data under evaluation are not random numbers but actual observations on nature.

The HiP grant was introduced and withdrawn at the same time as other interventions that may have an impact on birth weight. Healthy Start is a means tested voucher scheme for pregnant women. If they are in receipt of certain benefits or under 18 years old, then they are eligible for free vitamins and vouchers to be spent on fruits and vegetables. This scheme replaced the means tested parts of the Welfare Food Scheme in the UK (including Scotland in 2006) and is still currently in place. During this period, there were policy changes in the optimal timing of first booking appointments due to changes in blood tests offered to pregnant women in the Pregnancy Screening Programme. These changes were first discussed in 2008 and had to be implemented by all Health Boards by March 2011.^67^
^68^ Early booking is a HEAT target of the Scottish Government (Health improvement for the people of Scotland, Efficiency and governance improvements, Access to services, Treatment appropriate to individuals H11.1).^69^ At least 80% of pregnant women in each SIMD quintile will have booked for antenatal care by the 12th week of gestation by March 2015.

A further piece of legislation that may affect birth weight is the introduction of the smoking ban in public places in Scotland in March 2006. Mackay *et al*^70^ reported a reduction in the prevalence of current smoking among women who conceived after the introduction of the legislation prohibiting smoking. They also reported a reduction in small and very SGA, as well as in absolute LBW after the legislation. We will carry out a further analysis restricting the preintervention HiP grant period to April 2006 to March 2009.

It is possible that harm may have occurred due to the cash transfer. The £190 was given to pregnant women with no restriction as to how it should be spent, and we do not know how the money was used. We are examining how the intervention group differed; birth weight could have reduced or increased. We will carry out two-sided hypothesis tests to ensure that we are able to detect any such potential harmful effect.

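### As planned, the grant estimate for gestation at booking mixes the grant with an overlapping change in booking policy, because no model term or sensitivity analysis separates the two

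*Protocol article*

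**What the plan says.** The Introduction presents the grant as an attempt to change one behaviour, the appropriate and "timely receipt of antenatal care advice". Secondary outcomes opens its list with "Gestation at booking;Booking before 25 weeks". Study population sets the birth periods as January 2004 to March 2009, then "April 2009 to April 2011 (intervention) and May 2011 to December 2013 (postintervention").

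The Statistical analysis section warns that "The HiP grant was introduced and withdrawn at the same time as other interventions that may have an impact on birth weight". Among these it says that "there were policy changes in the optimal timing of first booking appointments" because of changes in pregnancy screening, and adds: "These changes were first discussed in 2008 and had to be implemented by all Health Boards by March 2011". It also cites a government target: "At least 80% of pregnant women in each SIMD quintile will have booked for antenatal care by the 12th week of gestation by March 2015".

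The same section gives the model as segmented or on/off regression with trend and season, births nested in mothers, "with mothers themselves clustered within data zones and Health Boards". In Table 2 both booking outcomes are adjusted for date of birth, the grant, maternal and obstetric factors, the income domain of the deprivation index and urban/rural status. There is no policy term. Three sensitivity analyses widen the grant window before, after, or on both sides, with dilution expected if the effect is the grant's.

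**The concern.** The overlapping policy is discussed only as something that may affect birth weight. It bears more directly on gestation at booking, since booking time is what it set out to change. A national time trend plus a national grant term cannot absorb a policy that arrives around the same time and then stays. A Health Board random effect removes fixed differences between Boards, not a change over time within them.

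Gestation at booking is the planned outcome nearest to the behaviour the grant targeted. If the window estimate is read as the grant's effect, the report could credit the grant with earlier booking that the screening policy produced, or could hide a real grant effect.

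**Working it through.** The plan states no figure on this point to reproduce, so the check is of dates first and then of what the planned models return.

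**1. Overlap.** The birth periods contain 63, 25 and 32 months (120 in all). Taking the policy span as January 2008 to March 2011, 24 of the 25 grant months fall inside it by month of birth. If booking is about 6 months before birth, the grant births were booked from October 2008 to October 2010, and 25 of 25 fall inside.

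**2. What the planned models return when the grant does nothing.** These assumptions are not in the document: the policy moves booking 7 days earlier at full roll-out, it persists, roll-out is linear from month s to month e, and booking is 6 months before birth. The noise-free outcome in birth month t is

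y(t) = -7 × F(t - 6), with F(b) = (b - s + 1)/(e - s + 1), held between 0 and 1.

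Two least-squares fits on the 120 months:
- Single dummy: intercept, linear trend, calendar month, D (D = 1 for April 2009 to April 2011).
- Segmented: the same, plus D × months since April 2009, a post-withdrawal level and a post-withdrawal slope.

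The true grant effect is 0. Estimates in days (negative = earlier booking):

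| Assumed roll-out | Single dummy | Segmented: level | Segmented: slope per year | Segmented: one year in | Segmented: post-withdrawal level |
|---|---|---|---|---|---|
| July 2008 to June 2009 | -2.2 | -4.15 | -1.76 | -5.9 | -6.7 |
| January 2008 to March 2011 | +0.1 | -1.37 | -1.98 | -3.4 | -6.1 |
| January 2010 to March 2011 | +2.9 | +1.06 | -2.09 | -1.0 | -6.5 |

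The one-year value is level plus slope, for example -4.15 - 1.76 = -5.9. Lags of 5 and 7 months give similar values. All sizes scale with the assumed 7 days.

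**3. The planned window-widening check.** Under the first roll-out, the false single-dummy estimate goes from -2.2 to -1.8 (3 months added on each side) to -1.4 (6 months). That shrinkage is what the plan would read as support for the grant. Under the second, it stays at about +0.1. Neither pattern identifies the policy as the cause.

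**4. Coding of a policy indicator.** The booking date is conception date plus gestation at booking, so it contains the outcome: late bookers are more often coded as booking after the change. A simulation with no true policy or grant effect (assumed 14 Boards, staggered dates, booking SD 14 to 28 days) gave a false policy coefficient of about +0.8 to +3 days with booking-date coding, and about 0 when coded at a fixed gestation. The grant coefficient moved by less than 0.1 day in that set-up.

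**The case against.** The strongest reply is that the design already holds evidence to tell the two apart. The grant was withdrawn and 32 months of births follow. A pure grant effect should reverse after April 2011; a lasting policy should not. The table bears this out: with no grant effect, the post-withdrawal level stays at -6.1 to -6.7 days. So a reader who infers that gestation at booking can show nothing about the grant goes too far. But the plan does not state this contrast as a test, allows for carryover after withdrawal (discussed for birth weight), and cites an early-booking target that could blur a reversal.

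A reader might also infer that the policy was phased in Board by Board across the grant's dates. The document gives only the year of first discussion and a deadline. Start dates, staggering and permanence are assumptions here.

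A third tempting reading is that the plan is inconsistent because the smoking ban gets its own restricted analysis. That ban has one date, before the grant window, so restricting the pre-period is possible; the booking change offers no equivalent.

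Finally, the policy is openly disclosed, Table 2 lists covariates to be considered, and a fuller plan may exist. That has some weight. Yet the article presents Table 2 as its analysis plan for outcomes and covariates, and the sensitivity analyses it does fix for attribution leave this problem untouched.

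**Conclusion.** The point holds in limited form. As planned, the window estimate for gestation at booking does not separate the grant from the booking policy. Under the 7-day assumption with no grant effect, the single-dummy estimate ranges from about -2 to +3 days, and the segmented model shows false earlier booking of 1.0 to 5.9 days one year into the window. These sizes are illustrative; under the longest roll-out tried, the single dummy is nearly unbiased. What does not depend on the 7 days is that the bias can take either sign according to dates that the model does not use.

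Booking before 25 weeks is probably less affected. The calculation says nothing about the primary outcome, birth weight.

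**What to change.** - For gestation at booking and booking before 25 weeks, obtain each Health Board's implementation date and add a Board-specific policy indicator. Code it at a fixed gestation: 1 if the pregnancy reached a set week on or after that Board's date. That date follows from date of birth and gestational age at delivery, both already study variables. Do not code it on the actual booking date.
- State that the report will show whether any change in gestation at booking reverses after withdrawal, and note that carryover and the early-booking target may blur this.
- If the dates cannot be obtained, or Boards started together, state that a change in gestation at booking will be reported as the joint effect of grant and policy, not attributed to the grant alone.

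The cost is one date per Board, whose availability the document does not establish, and one covariate. Some precision is lost if Boards started close together. The fallback costs one sentence.

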We will conduct sensitivity analyses to increase the probability that any observed effect can be attributed to the HiP grant. The timing of the HiP grant is well-defined and fixed, therefore using the interrupted time-series approach any effects within that window can be observed. We plan to carry out three analyses for this.
We will extend this window for some months before April 2009 (births before the HiP grant was introduced).We will extend this window for some months after April 2011 (births after the HiP grant was withdrawn).We will extend the window both before and after the HiP grant period. In each case we would expect to see a dilution of any effects of the HiP grant.

The statistical analysis plan detailing the outcomes and the covariates, which will be considered for adjustment in the statistical models are presented in table 2.

**Table 2 BMJOPEN2014006547TB2:** Analysis plan detailing the outcomes and the covariates that will be considered for adjustment in the statistical models

	Primary outcome	Secondary outcomes										
	Birth weight	Booking status		Measures of stage			Measures of size:	Other birth outcomes				Maternal smoking during this pregnancy
		Gestation at booking	Booking before 25 weeks	Gestational age at delivery	Term at birth	Weight-for-dates	Head circumference,	Mode of delivery	Stillbirth	5 min Apgar score	Neonatal death	
Covariates							Crown to heel length					
*I. Measured covariates*												
A. Sociodemographic determinants												
A-1. Related to the baby												
Date of birth	Χ	Χ	Χ	Χ	Χ	Χ	Χ	Χ	Χ	Χ	Χ	Χ
Sex	Χ			Χ	Χ	Χ	Χ	Χ	Χ	Χ	Χ	
Gestational age at delivery	Χ						Χ	Χ	Χ	Χ	Χ	
Birth weight							Χ			Χ	Χ	
Mode of delivery										Χ	Χ	
A-2. Related to the mother												
Hip grant	Χ	Χ	Χ	Χ	Χ	Χ	Χ	Χ	Χ	Χ	Χ	Χ
Age	Χ	Χ	Χ	Χ	Χ	Χ	Χ	Χ	Χ	Χ	Χ	Χ
Weight at booking	Χ	Χ	Χ	Χ	Χ	Χ	Χ	Χ	Χ	Χ	Χ	
Height	Χ			Χ	Χ	Χ	Χ	Χ	Χ	Χ	Χ	
Ethnic group	Χ	Χ	Χ	Χ	Χ	Χ	Χ	Χ	Χ	Χ	Χ	Χ
Parity	Χ	Χ	Χ	Χ	Χ	Χ	Χ	Χ	Χ	Χ	Χ	Χ
Marital status	Χ	Χ	Χ	Χ	Χ	Χ	Χ	Χ	Χ	Χ	Χ	Χ
Social class	Χ	Χ	Χ	Χ	Χ	Χ	Χ	Χ	Χ	Χ	Χ	Χ
B. Medical risks of the current pregnancy and before pregnancy												
Diabetes	Χ	Χ	Χ	Χ	Χ	Χ	Χ	Χ	Χ	Χ	Χ	
Hypertension	Χ	Χ	Χ	Χ	Χ	Χ	Χ	Χ	Χ	Χ	Χ	
Infection	Χ			Χ	Χ	Χ	Χ	Χ	Χ	Χ	Χ	
Congenital anomalies	Χ			Χ	Χ	Χ	Χ	Χ	Χ	Χ	Χ	
Induction of labour									Χ	Χ	Χ	
Duration of labour									Χ	Χ	Χ	
C. Medical risks related to previous pregnancies												
Previous spontaneous abortions		Χ	Χ						Χ			
Previous stillbirths		Χ	Χ						Χ			
Previous neonatal deaths		Χ	Χ								Χ	

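### The three window extensions test only whether an effect's timing fits the grant period, and only weakly; dilution should not be read as attribution to the grant, and placebo windows should be added

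*Protocol article*

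**What the plan says.** The sensitivity analyses are in the protocol article, Data analysis plan, Statistical analysis. Their purpose is stated as: "We will conduct sensitivity analyses to increase the probability that any observed effect can be attributed to the HiP grant". The argument is that the grant's dates are fixed and "therefore using the interrupted time-series approach any effects within that window can be observed". Three refits follow. The first moves the start of the window some months earlier and the second moves its end some months later. The third is described as: "We will extend the window both before and after the HiP grant period". The predicted result is: "In each case we would expect to see a dilution of any effects of the HiP grant".

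Just before this, the same section names the threat: "The HiP grant was introduced and withdrawn at the same time as other interventions that may have an impact on birth weight". It then dates three rivals: Healthy Start (2006, still running), changes to the timing of the booking appointment (discussed from 2008, in place by March 2011) and the smoking ban (March 2006).

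Study population gives the periods, which come to 63 months before, 25 during and 32 after the grant.

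**The concern.** A check on attribution should come out differently when the grant caused the effect and when something else did. The predicted dilution does not do so for two important alternatives. A cause switched on and off on the grant's own dates is diluted by exactly the same factor. A chance high run inside the window also shrinks, on average, once neighbouring months are added.

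The inference matters because the Implications section says a positive result could lead to recommending that a universal cash transfer be reintroduced. The sections on design and sensitivity analysis mention no unexposed comparison series, so much of the support for attribution has to come from timing.

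**Working it through.** **Inputs from the article.** 120 months (63 + 25 + 32); a 0/1 intervention dummy (the simplest model described); adjustment for trend and season; power 0.90 for 7 g at the two-sided 5% level.

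**Assumptions.** Extensions of 3 and 6 months, since the article says only some months; equal births per month; independent errors; linear trend. The article gives no birth-weight SD, so the 7 g figure is used only to set the scale: SE = 7/(1.960 + 1.282) = 2.16 g. The article gives no figure for the dilution, so there is none to reproduce.

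**Formulas.** Let M remove intercept, trend and calendar month, let x0 be the grant window and xE an extended window. Then

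- estimates: b0 = x0'My / x0'Mx0 and bE = xE'My / xE'MxE
- dilution factor: r = xE'Mx0 / xE'MxE
- variance ratio: q = x0'Mx0 / xE'MxE
- SE of (b0 − bE) = SE × √(1 + q − 2r)

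An effect d confined to the window, whatever its cause, gives expected values d and r·d. With no effect, the expected value of bE given b0 is also r·b0, so chance shrinks by the same factor.

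**A 7 g effect with the grant's dates, from any cause**

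| Extension | r | Estimate (g) | Drop (g) | SE of drop (g) | Drop/SE |
|---|---|---|---|---|---|
| 3 months before | 0.898 | 6.28 | 0.72 | 0.79 | 0.90 |
| 3 months after | 0.908 | 6.36 | 0.64 | 0.79 | 0.81 |
| 3 months both | 0.818 | 5.72 | 1.28 | 1.09 | 1.17 |
| 6 months before | 0.806 | 5.64 | 1.36 | 1.08 | 1.26 |
| 6 months after | 0.830 | 5.81 | 1.19 | 1.09 | 1.10 |
| 6 months both | 0.678 | 4.75 | 2.25 | 1.44 | 1.56 |

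No drop reaches twice its own SE.

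**Causes with other dates (3-month extensions)**

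| Profile | Main estimate | Before / after / both |
|---|---|---|
| 10-unit ramp, January 2008 to March 2011, then kept | 1.16 | 0.89 / 1.43 / 1.15 |
| 10-unit step from April 2006, kept | 1.18 | 1.47 / 1.03 / 1.32 |
| Smooth quadratic left after a linear trend | 3.38 | 3.65 / 3.35 / 3.61 |
| July 2008 to December 2011 | ratio 1 | 1.06 / 1.06 / 1.11 |
| Step from April 2009, never withdrawn | ratio 1 | 0.77 / 0.995 / 0.775 |

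The first four each rise in at least one extension. The last differs from the grant pattern chiefly in barely falling in the after extension. On a 7 g estimate that difference is 7 × (0.995 − 0.908) = 0.61 g, against an SE of 0.79 g.

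**How often all three estimates shrink.** The estimates were simulated from their joint normal distribution (4 million draws), keeping significant positive main estimates.

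| Extension | True 7 g effect | No effect | Ratio |
|---|---|---|---|
| 3 months | 67% | 54% | 0.67/0.54 = 1.24 |
| 6 months | 81% | 66% | 0.81/0.66 = 1.2 |

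The no-effect column does not depend on the SE, because every quantity in it scales with the SE. So even if a real effect always passed, the ratio could not exceed 1/0.54 = 1.9 (3 months) or 1/0.66 = 1.5 (6 months).

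**The case against.** A reader might infer that the extensions are useless for their stated purpose, that any departure from trend is diluted whatever caused it, or that the check nearly always passes. The documents and the calculation do not support any of these.

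- The stated aim is only to raise the probability of attribution. The article does not say that dilution proves causation.
- The rivals it dates do not share the grant's on and off dates. A 2006 step grows when the window is extended backwards, a 2008 to 2011 ramp grows when it is extended forwards, and a smooth quadratic grows in two of the three extensions. The check therefore has some power against the named rivals and against smooth curvature.
- A pass is not near-certain. A genuine 7 g effect fails to shrink in all three extensions 19% to 33% of the time (100 − 81 and 100 − 67).
- Other safeguards sit alongside: the baseline restricted to April 2006 onwards, the primiparous-only analysis, covariate adjustment, and the use of both introduction and withdrawal.

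All of this stands, and it limits the point to what a pass can show. It does not answer the case of a cause with the grant's own dates, which the article's general statement about other interventions raises, or the case of chance.

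**Conclusion.** The concern holds in a limited form. Dilution in the three extensions is evidence that an effect's timing matches April 2009 to April 2011. It can count against causes with clearly different dates. It carries no information on a cause with identical dates. Against chance it has a likelihood ratio of about 1.2 at the article's own power figure, and under 2 at any SE.

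These sizes rest on the assumed 3- and 6-month extensions, equal monthly births, independent errors, a linear trend and the simple dummy model. The equal dilution of a cause with the same dates is algebraic and needs none of the numerical assumptions. This is a worthwhile, inexpensive improvement; it does not invalidate the primary analysis.

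**What to change.** 1. Keep the three extensions, but describe dilution as evidence of timing specificity and not of attribution to the grant.
2. Add placebo windows. Refit the same model with false grant windows placed wholly in unexposed months (January 2004 to March 2009, and May 2011 to December 2013), and report where the real estimate falls among them.
3. State what this covers: chance, autocorrelation and unmodelled drift, but not a cause exactly coincident with the grant.

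The cost is extra runs of an existing model on data already held. The reference distribution will be coarse. A 25-month window has 63 − 25 + 1 = 39 monthly starting positions before the grant and 32 − 25 + 1 = 8 after it, and most of these overlap heavily. Shorter windows would give more positions after withdrawal but less precise estimates. Placebo windows around March 2006 may pick up the smoking ban, and those after April 2011 may pick up the carryover that the article anticipates; both should be noted when the distribution is read.

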### Outcome measures

#### Primary outcome

The primary outcome will be birth weight among singleton births. This is influenced by many factors including maternal nutrition and one of the intentions of the HiP grant was to improve this.

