D. Environmental and behavioural risks												
Income domain of the SIMD	Χ	Χ	Χ	Χ	Χ	Χ	Χ	Χ	Χ	Χ	Χ	Χ
Urban/rural status of the area of residence	Χ	Χ	Χ	Χ	Χ	Χ	Χ	Χ	Χ	Χ	Χ	Χ
Booking status (gestational age at booking, booking before 25 weeks)	Χ			Χ	Χ	Χ	Χ	Χ	Χ	Χ	Χ	Χ
Smoking status (before and during this pregnancy)	Χ	Χ	Χ	Χ	Χ	Χ	Χ	Χ	Χ	Χ	Χ	
Typical weekly alcohol consumption (before and during this pregnancy)	Χ	Χ	Χ	Χ	Χ	Χ	Χ	Χ	Χ	Χ	Χ	Χ
Drug misuse during this pregnancy	Χ	Χ	Χ	Χ	Χ	Χ	Χ	Χ	Χ	Χ	Χ	Χ
*II. Unmeasured covariates*												
Maternal weight gain												
Maternal nutrition												
Maternal education												
Maternal exposure to stress												
Maternal physical activity												
Exposure to toxic substances												
Birth interval												
History of preterm birth												
Statistical methods												
Multilevel linear regression	Χ	Χ		Χ			Χ					
Multilevel binomial logistic regression			Χ			Χ			Χ		Χ	Χ
Multilevel multinomial logistic regression					Χ			Χ		Χ		

Χ: variables which will be considered for adjustment in the statistical analysis.

SIMD, Scottish Index of Multiple Deprivation.

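### Table 2 offers birth weight, the primary outcome, as a covariate for head circumference and crown to heel length; if it is used, the grant coefficient is no longer the total effect on size.

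*Protocol article*

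**What the plan says.** All places are in the protocol article.

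- **Primary outcome:** "The primary outcome will be birth weight among singleton births". On birth weight and the purpose of the grant the article adds: "This is influenced by many factors including maternal nutrition and one of the intentions of the HiP grant was to improve this". Birth weight is therefore downstream of the grant.
- **Secondary outcomes:** the list includes "Measures of size: crown to heel length, head circumference", as outcomes in their own right.
- **Statistical analysis, Table 2:** the table is introduced as giving "the outcomes and the covariates, which will be considered for adjustment in the statistical models are presented in table 2". Its birth weight row is marked under three outcome columns: measures of size (one column shared by head circumference and crown to heel length), 5 min Apgar score and neonatal death.
- **Table 2 footnote:** a mark denotes "variables which will be considered for adjustment in the statistical analysis". It is a candidate, not a commitment.
- **Statistical analysis, text:** the list of adjustments for all analyses (temporal trend, season, and maternal, child and area factors) does not name birth weight. The models are described thus: "Multilevel univariable and multivariable models will be used to determine whether the outcomes changed".

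The article nowhere describes the size models as mediation or body-proportion analyses.

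**The concern.** Birth weight, head circumference and length are recorded on the same baby at birth, after the grant. All three measure size, and birth weight is the one the grant was expected to raise. A model for head circumference that holds birth weight fixed compares babies of equal weight inside and outside the grant period. Its grant coefficient then says whether heads are large or small for the weight, not whether the grant changed head size.

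The stated question is whether each outcome changed while the grant was in effect. Under this adjustment a real, proportionate gain in size could be reported as no effect, and a real but smaller gain as a reduction. The size results would then seem to contradict a favourable birth-weight result only because of what was conditioned on.

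**Working it through.** **1. Which columns are marked.** Reading the birth weight row against the twelve outcome columns puts the marks in column 7 (measures of size), column 10 (Apgar) and column 11 (neonatal death), and in no others.

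**2. What the coefficient becomes.** Let *t* be the total grant effect on the size measure, *d* the grant effect on birth weight, and *b* the slope of the size measure on birth weight given the other covariates. In a linear model,

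adjusted grant coefficient = *t* − *b* × *d*.

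- Proportional gain, *t* = *bd*: coefficient 0.
- Half-proportional gain, *t* = *bd*/2: coefficient −*bd*/2, the opposite sign to the truth.
- No change in size, *t* = 0: coefficient −*bd*.
- *t* greater than *bd*: coefficient positive, so a gain still shows.

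**3. Numerical check of the identity.** The article gives no SDs or correlations. Assumed values: birth weight SD 550 g, head circumference SD 1.5 cm, correlation 0.7. Take *d* = 50 g, the size of the context figure under Sample size. Then *b* = 0.7 × 1.5/550 = 0.00191 cm per g and *bd* = 0.095 cm. Ordinary least squares on 585 000 simulated births, 25/120 of them exposed, gave:

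| True effect on head circumference | Without birth weight | With birth weight |
|---|---|---|
| +0.095 cm (proportional) | +0.102 | +0.003 |
| +0.048 cm (half) | +0.044 | −0.048 |
| 0 | −0.007 | −0.104 |

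The model without birth weight recovers the truth within sampling error. The model with it follows *t* − *bd*.

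**4. How often a false reduction would be significant.** The article has no power figure for the size measures, so the starting point is its birth-weight statement: 7 g at power 0.90, two-sided 5%. This implies SE = 7/(1.960 + 1.282) = 2.16 g and a standardised effect of 3.24. The statement itself cannot be strictly reproduced, because no birth weight SD is given.

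With *c* the proportion with data, *r* the correlation of the size measure with birth weight given the other covariates, and the same clustering inflation, the SDs cancel. For no true change in size:

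*z* = −3.24 × √*c* × *r*/√(1 − *r*²), and P(significant reduction) = Φ(|*z*| − 1.96).

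Sample size gives 12% missing for head circumference (*c* = 0.88, so 3.24 × √0.88 = 3.04) and 15% for length (*c* = 0.85). For a half-proportional gain, *z* is halved.

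| *r* (assumed) | *r*/√(1−*r*²) | \|*z*\|, head, no change | P, head, no change | P, length, no change | P, head, half-proportional gain |
|---|---|---|---|---|---|
| 0.4 | 0.436 | 1.33 | 26% | 26% | 10% |
| 0.5 | 0.577 | 1.76 | 42% | 41% | 14% |
| 0.6 | 0.750 | 2.28 | 63% | 61% | 21% |
| 0.7 | 0.980 | 2.98 | 85% | 83% | 32% |
| 0.8 | 1.333 | 4.05 | 98% | 98% | 53% |

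The nominal rate in that direction is 2.5%. For a fully proportional gain the false-reduction rate is nominal, but the true gain disappears.

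**The case against.** **The marks are only candidates.** This stands as to wording: Table 2 and its footnote say considered, and the list for all analyses leaves birth weight out. A reader might infer that the adjustment is fixed; the article does not say so. But the text list also omits other variables marked for the size measures, such as gestational age at delivery and hypertension. Its silence therefore does not show that birth weight will be left out. Birth weight would predict head size and length strongly, so selection by fit would tend to keep it.

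**Estimates without birth weight are planned.** This stands in part. Univariable models omit birth weight, and the simplest model is described as the intervention indicator with adjustment for relevant factors. The univariable results lack the planned confounder adjustment, so they soften the problem without curing it.

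**These models could still show a size effect.** This stands. A reader might infer that they cannot; that is too strong. An effect larger than birth weight predicts would remain visible.

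**The harm argument is stretched.** This stands. The article says "We will carry out two-sided hypothesis tests to ensure that we are able to detect any such potential harmful effect", but that paragraph discusses birth weight rising or falling and does not name head circumference or length as harm endpoints. A reader might infer that the plan would report a false harm. The supportable statement is narrower: a negative size coefficient could be misread, although the birth-weight result would be reported beside it.

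**The magnitude is an extreme case.** This also stands. No change in head circumference is the least favourable assumption, and the article presents 7 g as an indication of power, not as an expected effect. The relevant correlation is conditional on gestational age, sex and maternal height, all marked for this column, so it may lie toward the lower end of the range.

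**Conclusion.** The point holds in a limited form. Birth weight should not be a candidate covariate for head circumference and crown to heel length when the question is whether the grant changed them. If it is used, the coefficient is the total effect less the part predicted by birth weight. The direction of the distortion follows from a positive correlation and a positive grant effect on birth weight. If the grant does not change birth weight, there is no distortion.

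Its size cannot be fixed from the article. On a 7 g birth-weight gain, the chance of a significant false reduction in head circumference runs from 26% to 98% with no true change, and from 10% to 53% with a half-proportional gain, for conditional correlations of 0.4 to 0.8. These correlations are assumptions.

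Two secondary outcomes are concerned, and the primary analysis is unaffected. The same row also marks Apgar score and neonatal death, which likewise arise after the grant. They are not assessed here, and this point should not be read as a ruling on them.

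**What to change.** 1. In Table 2, remove birth weight from the candidate covariates for the measures of size. This agrees with the text list of adjustments for all analyses.
2. State that the reported result for each size measure is the confounder-adjusted total grant effect.
3. If body proportion is of interest, report a birth-weight-adjusted model separately, label it as such, and do not use it as evidence on size or harm.

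The cost is one mark in a table and some precision. Leaving birth weight out multiplies the standard error of the size models by 1/√(1 − *r*²), which is 1.09 at *r* = 0.4 and 1.67 at *r* = 0.8. With over 585 000 births expected, that is a minor price for an estimate that answers the stated question.
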